### Study population

2.3

We will recruit 600 participants using a stratified random sampling based on the 2021 census sections. The sampling will be stratified by census section, sex, age group to ensure its representativeness using population quotas from census data provided by Spain's National Statistics Institute (INE, Supplementary Table S1)(10). Furthermore we will apply an overall migrant quota of 25.6%. By using a stratified sampling, we ensure a representative sample of the neighbourhood's population, also in terms of representativeness of men and women across age groups for each of the different census sections that compound the District 2 of Elche. Furthermore, given that representativeness is a challenge for any population survey, targeted outreach through social media, local traditional media and community-based engagement activities will be employed to increase community awareness and improve response rates.

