### Sample size estimation and selection criteria

2.4

The sample size has been calculated assuming that the prevalence of the variables of interest (e.g. proportion of individuals with poor health-related quality of life, proportion of individuals with limited critical health literacy etc.) does not exceed 30%, with an absolute precision of ± 5% and a confidence level of 95%. A design effect of 1.5 has been applied, following the recommendations of the World Health Organization's (WHO) STEPS guidelines (13) for complex designs. In addition, a rejection rate of up to 20% has been considered, implying the need to recruit at least 590 participants. The proposed inclusion of 600 participants also ensures the estimation of indicators for specific subgroups (such as by sex) with an absolute precision of close to ± 5%.

A before-and-after analysis will be conducted with 600 independent participants at each time point, selected using comparable samples and applying the same inclusion criteria and sampling design. This sample size is sufficient to detect significant differences in both our main outcome (i.e., health-related quality of life) and secondary variables. In the case of health-related quality of life, it allows us to identify absolute changes of around 10%, with a confidence level of 95% and a statistical power close to 80%. The exact power will depend on the initial prevalence of the indicator and the magnitude of the observed effect. Although the analysis of social inequalities may have lower power due to stratification by subgroups, we estimate that the sample size will be sufficient to identify relevant trends and significant differences in social inequalities in the studied sample.

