### Data analysis

2.8

As main outcome, the mean and the standard deviation of the health-related quality of life will be calculated and stratified by sex, age group and other sociodemographic variables, thus allowing for an equity analysis. In addition, we will perform multivariate models to analyse the association of sociodemographic characteristics on health-related quality of life and secondary variables (critical health literacy, social capital, community capital, and knowledge, attitudes and practices on personal antibiotic use). These results will be also crucial to enrich the discussions in the co-creation process, facilitating an equitable and contextualized approach to the identified health issues. A before-and-after analysis will also be carried out using the population-based survey data to assess changes across time points (pre- and post-intervention) in the population in both main and secondary variables, providing evidence on the evolution of health-related quality of life and other relevant social determinants of health. Specifically, firstly, the normal distribution of physical and mental HRQoL will be tested by conducting Shapiro-Wilk tests and plotting histograms. In case of observing a non-normal distribution, these variables will be dichotomised using the median value of the whole sample (pre- and post-intervention). Therefore, given the distribution of health-related quality of life, multivariate linear regression models or Poisson regression models with robust standard errors will be used to estimate absolute and relative changes across time points. Additional models will be run, including interaction terms of time with sex, age group and other sociodemographic variables to assess the changes in social inequalities in HRQoL. Contextual variables will be included, such as economic development, unemployment rate and poverty rate at the regional level of the province of Alicante before and after the intervention, retrieved from the National Institute of Statistics (INE) and the statistics portal of the Valencian Community in Spain. Statistical analysis will be adjusted for sex, age group and other sociodemographic variables such as education, ethnicity, migration status, household income, employment status and marital status, among others. Multiple imputation will be used for missing data on HRQoL and secondary variables. For the remaining covariates, an additional category of missing values will be created to include these individuals in the statistical analyses.

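### Missing covariates get a 'missing' category while outcomes are multiply imputed: a small, avoidable bias in the before-after estimate and a more direct distortion of the equity contrasts

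*Protocol article*

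**What the plan says.** Section 2.8 (Data analysis) sets two rules. For outcomes: "Multiple imputation will be used for missing data on HRQoL and secondary variables". For everything else: "For the remaining covariates, an additional category of missing values will be created to include these individuals in the statistical analyses". It gives no reason for treating the two differently.

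The covariates under the second rule have two jobs in the same section. They are the adjustment set, since the analysis is "adjusted for sex, age group and other sociodemographic variables such as education, ethnicity, migration status, household income" and so on through employment and marital status. They are also the axes of the equity analysis, through further models "including interaction terms of time with sex, age group and other sociodemographic variables to assess the changes in social inequalities in HRQoL".

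On design, section 2.4 says "A before-and-after analysis will be conducted with 600 independent participants at each time point". Section 2.3 says "The sampling will be stratified by census section, sex, age group", and adds "we will apply an overall migrant quota of 25.6" per cent. No quota covers education, income, employment or marital status. Section 2.7 has participants complete the sociodemographic items themselves at the start of the interview, with help on request. The article gives no expected rate of missing covariates.

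**The concern.** An added 'missing' category does no harm to an effect estimate when randomisation balances the covariates. Here nothing is randomised. The contrast is between two separate samples taken years apart, and the covariates outside the quotas can differ between them. For someone whose income is unknown, the model adjusts for the fact that it is unknown, not for income. If the income mix has changed between waves, that part of the sample carries the change straight into the time coefficient.

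The second job matters more. Equity is a declared aim, and baseline gradients are meant to steer the co-creation work. A person who does not report income or education is moved out of the ordered groups into one that has no social position. Adjusting the education contrast for an incompletely controlled income variable, or the reverse, also changes that contrast.

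**Working it through.** The article has no figure of its own on this point, so there is nothing to reproduce. The one input from it is 600 per wave. The other values below are assumptions.

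**1. Before-after estimate, one binary confounder, missing completely at random.** Assume prevalence 40% in wave 1 and 50% in wave 2, effect 0.5 SD, no true time effect and equal waves. The crude bias is 0.5 × (0.50 − 0.40) = 0.050 SD.

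With a missing category, the OLS time coefficient is a weighted mean of the time differences within strata. Each weight is (share of sample) × π(1 − π), where π is the proportion of the stratum that belongs to wave 2. In the observed strata the difference is 0; in the missing stratum it is 0.050.

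With 25% missing:
- Observed, confounder absent: share 0.4125, weight 0.1023
- Observed, confounder present: share 0.3375, weight 0.0833
- Missing: share 0.25, weight 0.25 × 0.25 = 0.0625
- Bias = 0.050 × 0.0625 / (0.1023 + 0.0833 + 0.0625) = 0.050 × 0.252 = **0.0126 SD**

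With 5% missing the weights are 0.1295, 0.1056 and 0.0125, so bias = 0.050 × 0.0505 = **0.0025 SD**.

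Simulation of the same set-up (25 replicates of 200,000 per wave) gave, at 25% missing: crude 0.050, missing category 0.012, multiple imputation of the covariate −0.001, fully observed −0.001. At 5% the missing-category result was 0.002.

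**2. Size against precision.** SE of the wave difference = √(2/600) = 0.058 SD. So 0.0126 is 0.0126/0.058 ≈ 0.22 SE and 0.0025 is about 0.04 SE. A shift of 0.22 SE moves a nominal two-sided 5% test to about 5.5%.

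**3. Two correlated covariates.** Assume three-level income and education, each step worth 3 HRQoL points (high versus low = 6.0), residual SD 9, and a latent socioeconomic shift between waves of 0, 0.2 or 0.4 SD. Missingness is either completely at random or more frequent in low groups.

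| Missing (income / education) | Time-effect bias, no shift | 0.2 SD shift (crude about 0.6) | 0.4 SD shift (crude about 1.2) | Education contrast (true 6.0) |
|---|---|---|---|---|
| 5% / 2% | about 0 | 0.01–0.03 | 0.01–0.05 | 6.1–6.2 |
| 20–30% / 5–30% | about 0 | about 0.05–0.13 | about 0.1–0.3 | 6.4–6.8 |

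At 20–30% of income missing, roughly 8–24% of the crude confounding stays. The largest education contrast was 6.76, and 6.76/6.0 = 1.13, an inflation of 13%. This needs no shift between waves. The income contrast stayed at 5.9–6.0 until education was also 30% missing, when it rose to 6.4–6.6. With an SD of 10, the SE of the time effect is 10 × √(2/600) = 0.58 points.

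**4. Bias without a shift.** Take prevalence 45% in both waves. Let non-response be 15% throughout wave 1, and in wave 2 15% without the confounder and 35% with it. Among the missing, the confounder's prevalence is 0.45 in wave 1 and (0.45 × 0.35)/(0.45 × 0.35 + 0.55 × 0.15) = 0.656 in wave 2. The difference in the missing stratum is 0.5 × 0.206 = 0.103 SD. Its weight share is 0.0462/(0.1169 + 0.0829 + 0.0462) = 0.188, so bias = **0.019 SD**. In simulation of this case the missing category gave 0.020, complete cases about 0, and imputation assuming missing at random 0.031. If both waves keep the same ratio of non-response between groups (10% and 20%, then 20% and 40%), the bias is 0. Unequal rates alone do not create it.

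**The case against.** The case for leaving the rule alone rests on size, and much of it stands.

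- The sampling design already guards against compositional change: the same quotas at both waves for section, sex and age, and one for migrants. A reader might infer that regression adjustment is the only protection. Section 2.3 shows that it is not.
- Bias in the time effect is conditional. Without a shift, and without informative non-response that changes between waves, it is about zero.
- Nothing in the article supports 25% missing. The items come first, with an interviewer present. That does not rule out refusal of income.
- A reader might infer that the missing fraction of the confounding stays for every affected covariate. That holds for a single confounder. With correlated covariates, observed ones recover part of it.
- A reader might also infer that the gradients are flattened. The calculations show mostly inflation.
- Imputation relies on missing at random, which income refusal may break. Step 4 gives a case where imputation does worse than the missing category.
- The Discussion already asks for caution and frames results as time trends in the district.

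What does not stand is that this makes the rule sound. The method is stated, not left open; no reason is given for it; and the caveats in the Discussion do not address the equity contrasts.

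**Conclusion.** The point holds as a cheap improvement of minor to moderate severity. The planned rule leaves part of the confounding by education, income, employment or marital status in the before-after change whenever these are missing and their distribution shifts between waves. Bias can also arise without a shift if the dependence of non-response on the covariate differs between waves. Under the random-missingness assumptions above it is about 0.0025 to 0.0126 SD at 5% to 25% missing, well under a standard error of 0.058 SD. The article does not support a reading that the before-after result is invalidated.

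The equity analysis is the stronger reason to change. Non-reporters lose their social position, and mutually adjusted contrasts were off by up to about 13% in the assumed scenario with 20–30% of income missing, and by under 3% with 5% missing. All sizes rest on assumed missingness, shifts and effects; the baseline data will show the first of these.

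**What to change.** In section 2.8, put the adjustment and equity covariates into the same multiple-imputation model as HRQoL and the secondary variables. Include wave and, as far as 1,200 people allow, the planned time-by-group interactions. Keep the missing-category analysis as a sensitivity analysis. Add complete cases as a second one, since they were unbiased in step 4, where imputation was not. Report missingness of each covariate by wave.

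The cost is a reworded sentence, a larger imputation model and open reliance on missing at random, which may not hold fully for income. No new data are needed, imputation is already planned, and the second survey is not due until 2029.

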## Discussion

3

In a context of increasing medicalisation and an overburdened health system, non-pharmacological interventions based on community-based approaches are often relegated to the background, despite their proven efficacy at the population level (26). Although many health professionals recognize the potential and importance of these interventions for patients, they also point out that lack of time and accessible resources limit their implementation in daily practice (27, 28). Within this framework, the CAIR project will provide evidence to the growing recognition that improving health equity requires moving beyond individual-level interventions toward approaches that engage communities in defining and addressing their own priorities. The population-based surveys described here will allow us to assess the effect of the co-created intervention on health-related quality of life, critical health literacy, social and community capital, and knowledge, attitudes and practices on personal antibiotic use as well as their social inequalities across sociodemographic information.

HRQoL was selected as our primary outcome because it is increasingly recognized in epidemiological research as a robust indicator of morbidity and mortality, capturing not only physical health but also mental and social wellbeing (29, 30). Examining variations in HRQoL across sociodemographic groups will enable an equity-focused analysis and provide critical insights into the health of the local population. This information will be essential for assessing the effect of the co-created process for advancing toward health equity. The multidimensional structure of the VR-12 questionnaire further allows us to identify health-related inequalities across demographic characteristics and to evaluate changes in both physical and mental health domains after the intervention (31, 32).

We will also incorporate CHL into our analysis. According to WHO, strategies that focus on the design and implementation of interventions that address health inequalities should include an assessment of the health literacy of communities. Different domains of health literacy include basic functional health literacy (the ability to access, understand, appraise and apply health information), communicative health literacy and critical health literacy (15). In this project we are particularly concerned with CHL because it involves the critical appraisal of information, understanding the social determinants of health and is linked to collective action (18). Furthermore, improved critical health literacy is widely assumed to lead to a more effective and efficient use of services (17).

Additionally, we have designed a tool to measure community capital, considered a central dimension for understanding how local contexts shape opportunities for health and wellbeing. Building on the principles of salutogenesis and the assets-based community development literature (9, 19), our tool seeks to gather information that promotes the recognition and mobilization of the resources, relationships, and strengths that already exist within communities. However, previous research has shown that merely identifying or mapping community assets does not necessarily translate into meaningful change (8). Resources often remain underused when individuals face social, cultural, economic, or structural barriers to accessing them. These barriers are themselves socially patterned and can exacerbate inequities if not addressed. One of the innovative contributions of this study is the development of a tool that not only provides a quantitative picture of the community capital individuals perceive, but also captures the barriers they experience in practice and how these vary across population groups. We hope that this nuanced understanding will be particularly valuable for the cocreation of community initiatives within the CAIR project, enabling strategies that both strengthen community capital and actively tackle the obstacles that limit its equitable use.

Although social capital is included in the community capital scale described above, we added a more explicit focus on this dimension given its relevance as a key determinant of physical and mental health (33–35) and its influence on participation in community processes (36). Social capital can be conceptualized at both individual and community level. While cognitive social capital refers to people's perceptions about the level of interpersonal trust, sharing and reciprocity in their community, on the other hand, structural social conectiveness includes the density of one's social networks, and patterns of civic engagement (35). Furthermore, we can think of “bonding” capital when members of your network provide support in times of strife (e.g., cover costs in moments of need) or “bridging” capital when people in your network can help you improve your situation (e.g., relatives able to help you achieve goals). The tool proposed in this study includes items capturing assistance-related trust (e.g., receiving financial help in times of need), contact with similar or different people as an indicator of bridging social capital, and sub-section on community belonging and cohesion. Improving social capital and its different dimensions is a likely benefit from our project's research activity itself, and is a key determinant of physical and mental health (33, 34).

Finally, we included a questionnaire to measure KAP regarding antibiotics at the population level. This is directly relevant to the rational use of antibiotics and, consequently, to reducing the risk of AMR, which is recognized as one of the top ten threats to global public health (37). Although a comprehensive approach to AMR must also consider prescribing practices among professionals and antibiotic use, the overuse and misuse of antibiotics in the community remains a major driver of AMR, which requires urgent, coordinated action (38). Misconceptions about antibiotics are widespread, such as believing they are effective against viral infections or discontinuing treatment once symptoms improve (39). Existing communication and engagement initiatives often miss the most vulnerable and those most at risk of suffering the negative consequences of AMR (40). Therefore, reducing popular demand for antimicrobials is a key objective of any effective AMR strategy, and the KAP data collected here will help inform targeted, equity-oriented interventions within the CAIR project.

It is essential to adopt more holistic approaches that combine biomedical interventions with non-pharmacological strategies, promoting active community participation and addressing both the underlying causes of health problems and the social inequalities that shape them. The implications of the study are not only on analyzing the potential effects of co-created actions on health and health equity, but also on generating evidence to decision-makers that community-centered, intersectoral approaches may strengthen health system performance and contribute meaningfully to better outcomes at a population level.

The use of repeated population surveys is a strength of this study, as it enables the assessment of change over time through before-and-after comparisons of carefully selected indicators that are directly relevant to co-creation processes. However, an important limitation of the overall design is the absence of a control area where no co-creation activities are implemented. As this is not a controlled trial, we cannot fully disentangle the effects of the interventions from broader contextual changes occurring over the same period. Therefore, the results obtained from the before-and-after analysis should be interpreted with caution. Various external and contextual factors, such as other policy measures implemented for the general population, economic and social changes, or changes in access to healthcare, may also influence the evolution of our primary health outcome despite controlling for macro-level variables. Moreover, different, independent participants will be recruited at baseline and after the intervention, which also limits the effects attributable to the co-creation intervention process. In this regard, our analysis should be interpreted as time-trend changes in the Municipal District 2 of Elche where targeted cocreation is taking place rather than changes among individuals taking part in the cocreation intervention.

For the surveys themselves, we also recognize potential challenges related to the underrepresentation of migrant populations, particularly those in more vulnerable situations. In this sense, such population groups—particularly migrants and racialised populations—are more likely to report poorer health outcomes and if they are underrepresented in the sample, the resulting estimates may be biased upwards, overstating the overall health status of the population. To mitigate this, the role of cultural mediators will be crucial to ensure culturally competent engagement and reduce barriers to facilitate the participation of such groups and Arabic-speaking individuals.

## Conclusion

4

This protocol outlines the design of the population-based survey component of the CAIR study. The survey will provide essential baseline and post-intervention data to assess changes in key indicators of health-related quality of life, critical health literacy, social and community capital, and knowledge, attitudes, and practices on personal antibiotic use. Integrated within a participatory process of co-creation, the surveys will enable a before-and-after assessment of community-level changes and provide valuable insights into the measurement of health equity in complex, real-world settings.
